# 1 ADMINISTRATIVE INFORMATION

## 1.1 Title:

Effect of weight loss and liraglutide on neutrophil gelatinase-associated lipocalin (NGAL) levels among overweight patient with knee osteoarthritis (KOA): Secondary analyses for a randomized controlled trial

## Trial registration:

EudraCT Number: 2015-005163-16)

ClinicalTrials.gov identifier: NCT02905864

## SAP version:

1.0 (July 5th, 2023)

## Protocol version:

This document has been written based on information contained in the protocol V.2, 07th July 2021. The study is a secondary analysis of the LOSE-IT trial, with the protocol (V.6; 30 January 2017) “*Effect of liraglutide on body weight and pain in patients with overweight and knee osteoarthritis: protocol for a randomized, double-blind, placebo-controlled, parallel-group, single-centre trial*” (see: BMJ Open. 2019 May 5;9(5):e024065. doi: 10.1136/bmjopen-2018-024065) [1] and results published in the journal article “*Liraglutide after diet-induced weight loss for pain and weight control in knee osteoarthritis: a randomized controlled trial*” (*The American Journal of Clinical Nutrition*, Volume 113, Issue 2, February 2021, Pages 314–323, <https://doi.org/10.1093/ajcn/nqaa328>) [2].

### 3 PURPOSE

This statistical analysis plan (SAP) describes detailed aspects of data preparation and analysis and was set up before initiating the analyses.

## 4 INTRODUCTIONS

### 4.1 Background and rationale

The current global obesity pandemic is both the leading cause of soaring rates of metabolic diseases and important risk factor in the development of knee osteoarthritis (KOA) [3]. Moreover, obesity and overweight has been associated with a state of chronic low-grade inflammation. Efforts dedicated to the advancement of interventions for obesity and overweight have prompted an interest in adipocyte biology. Adipose tissues are now recognized as an endocrine organ capable of secreting a wide variety of adipose-derived factors – collectively termed "adipokines" [4]. Adipokines include a variety of proinflammatory factors, most of which are increased in obese individuals. Proinflammatory adipokines appear to contribute to the so-called "low-grade inflammatory state" found in overweight or obese individuals. The indication of increased prevalence of OA in the hands, i.e. non-weight bearing joints, suggests an importance of adipokines in OA [5–7]. The presence of the adipokine neutrophil gelatinase-associated lipocalin (NGAL) or lipocalin-2(LCN2) in osteoarthritic joints provides a possible connection between low grade inflammation in obese patients and increased OA. Emerging evidence shows that NGAL may contribute to the pathophysiology of KOA through its involvement in inflammatory process and cartilage turnover with earlier studies showing NGAL to stabilize cartilage degenerating enzymes [8,9]. This suggests a possible biochemical connection between obesity/overweight and OA. NGAL has emerged as a pleiotropic molecule, involved in a variety of physiological and pathophysiological processes such as metabolic homeostasis, apoptosis, infection, immune response, or inflammation with research suggesting a possible role of NGAL in the pathophysiology of rheumatic joint diseases and osteoarthritis (OA) [9,10]. Murine in vitro studies have shown that white adipose tissues (WAT) are a significant source of NGAL and are linked to key components of metabolic syndrome e.g. insulin resistance [11]. However, contrary to previous evidence, a diet/exercise study found that there was no difference in NGAL levels following diet intervention and/or exercise in overweight and obese patients participants [12]. This underlines the need for further research to determine if NGAL has an effect in the pathophysiology of OA.

Liraglutide, a newer GLP-1 analog, with a dual indication of type 2 diabetes and of weight loss, was recently tested in a population of (KOA) patients in a randomized controlled trial (RCT), i.e., the LOSE-IT trial [1,2]. In the LOSE-IT trial, adult patients with overweight or obesity and KOA were offered an initial 8-week intensive diet intervention (IDI) followed by a weight loss maintenance period in which participants who had at least attained a 5% weight loss of initial body mass were randomized to either liraglutide 3 mg or placebo for 52 weeks. Using data from the LOSE-IT trail we

wish to examine how serum NGAL responds to the initial 8-week IDI triggered weight loss and the subsequent 52-week liraglutide 3 mg vs. placebo weight-loss maintenance period.

### 4.3 Study Objectives

- *Primary objective:* To evaluate changes in serum NGAL in overweight individuals with KOA undergoing a significant ( $\geq 5\%$ ) weight loss from an IDI from week -8 (enrollment) to week 0 (randomization).
- *Secondary objective:* To compare the effect of liraglutide, relative to placebo on changes in serum NGAL from week 0 (randomization) to week 52 (end of trial), in individuals with KOA who have achieved a significant ( $\geq 5\%$ ) weight loss through the initial 8-week dietary intervention.
- *Exploratory objectives:*
  - To evaluate changes in [i] C-reactive protein (CRP), [ii] total-Cholesterol, [iii] high-density lipoprotein cholesterol (HDL), [iv] low-density lipoprotein cholesterol (LDL), [v] triglycerides (TG), [vi] glucose, [vii] glycated hemoglobin (HbA1c), [viii] creatinine, [ix] estimated glomerular filtration rate (eGFR), [x] alanine aminotransferase (ALAT), [xi] systolic blood pressure (BP), [xii] diastolic BP, [xiii] body weight and [xiv] BMI in overweight individuals with KOA who undergo a significant ( $\geq 5\%$ ) weight loss from an 8-week intensive dietary intervention.
  - To compare the effect of liraglutide, relative to placebo, on changes in [i] CRP, [ii] total-Cholesterol, [iii] HDL, [iv] LDL, [v] TG, [vi] glucose, [vii] HbA1c, [viii] creatinine, [ix] eGFR, [x] ALAT, [xi] systolic BP, [xii] diastolic BP, [xiii] body weight and [xiv] BMI, from baseline (week 0) to week 52, in overweight individuals with KOA who have achieved a significant ( $\geq 5\%$ ) weight loss through the initial 8-week dietary intervention.

### 4.4 Hypotheses

- a) The weight loss observed during the 8-week IDI (from week -8 [enrollment] to week 0 [randomization]) will result in a reduction of serum NGAL in overweight subjects with KOA.
- b) Liraglutide 3 mg is superior to placebo with respect to reducing serum NGAL from week 0 (randomization) to week 52 (end of trial).

## 5 STUDY METHODS

### 5.1 Trial design

The original trial design was a single-center, double-blinded, randomized, parallel-group, placebo-controlled trial. Treatment allocation was a 1:1 ratio. The trial contained two periods: All participants were initially enrolled in an 8-week IDI period (week -8 to 0) prior to randomization (see Figure 1 in Section 12: Tables and figures). If successfully achieving a minimum weight loss of 5% (baseline body weight) during IDI, participants were randomly allocated to either liraglutide 3 mg/day or an identically appearing placebo throughout the 52-week trial period (week 0 to 52). Both groups received a tapering dietary intervention (TDI) during the initial 8 weeks after randomization (week 0 to 8) [2].

### 5.2 Randomization

*As described in original trial protocol:*

Patients were randomized in a 1:1 manner to receive either 3 mg/day liraglutide or identically appearing placebo at week 0, i.e., after the initial 8-week intensive diet period. Stratified randomization was done based on sex (male vs. female), age (<60 years vs. ≥60 years), and obesity class (BMI; < 40 kg/m^2 vs. ≥ 40 kg/m^2) status at trial enrollment (week -8). A computer-generated randomization sequence was produced using SAS PROC PLAN to generate eight separate randomization schedules before any participant was enrolled, allocating participants in permuted blocks of 2 to 6 to the daily liraglutide 3 mg/day or placebo group. Allocation concealment was secure by utilizing the computer-generated allocation process (above) where the patient identifier was coupled to one of the experimental groups only if/when the physician clicked on the ‘randomization button’, appearing at the baseline visit (week 0, visit T0) in the eCRF system. Upon allocation to one of the two experimental groups, the patient identifier was automatically coupled to specific pens, each of them labeled by a single and unique Dispensing Unit Number (DUN) [1].

### 5.3 Blinding

Following randomization, the entire process was blinded for participants and investigators, clinical, academic, and administrative trial personnel.

## **5.4 Power and sample size**

The original trial was powered as follows: The co-primary outcomes were changes in body weight and KOOS-Pain from randomization to the end of the trial, 52 weeks after randomization. With two (co-primary) efficacy endpoints in a clinical trial, the trial's primary objective is met only if a statistically significant ( $p < .05$ ) beneficial effect is demonstrated on both endpoints. The sample size of 150 participants was designed to provide a reasonable power ( $>80\%$ ) to detect a 5.5 kg difference in body weight change between the groups, and an 8-units difference in the KOOS-Pain in the original trial [2]. All power and sample size analyses for the original trial were conducted using 'SAS Power and Sample Size', version 3.1 (SAS Institute Inc., Cary, North Carolina) [2].

## **5.5 Framework**

This is a superiority trial both concerning primary and secondary outcome. The null hypothesis of the primary outcome is no change in serum NGAL following weight loss. For the secondary outcome null hypothesis is that liraglutide is not different from placebo with respect to changes in serum NGAL concentration.

## **5.6 Statistical interim analyses and stopping guidance**

Since there were no interim analyses performed in the original trial, this was not applied in this current study.

## **5.7 Timing of final analysis**

Not applicable. Secondary analyses to an already published trial.

## **5.8 Timing of outcome assessments**

The outcomes investigated in this trial are assessed at weeks -8, 0, and 52.

# **6 STATISTICAL PRINCIPLES**

## **6.1 Confidence intervals and P values**

*Level of statistical significance and use of confidence intervals:* All applicable statistical tests will be two-sided and will be performed using a 5% significance level. All confidence intervals presented will be 95% and two-sided.

*Rationale for any adjustment for multiplicity:*

Due to the explorative design of this study, we will not adjust for multiplicity in this study. P values will be reported for all analyses, while the interpretation will be based on the hierarchy of which these will be analyzed as indicated by the order of outcomes in the objectives.

## **6.2 Analyses populations**

We will analyze all patients randomized at week 0 regardless of their eligibility or adherence during the original trial but with NGAL data available at enrollment (week -8). This is a modified intention-to-treat (mITT) population of the original ITT population in the LOSE-IT trial.

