### **7.2 Eligibility**

Inclusion criteria in the original trial as described in suppl. material *Am J Clin Nutr* 2021;**113**:314–23. doi:10.1093/ajcn/nqaa328 [2]:

- Informed consent obtained
- Clinical diagnosis of knee OA (American College of Rheumatology [ACR] criteria) with early to moderate radiographic changes (Kellgren-Lawrence [KL] grades 1, 2, or 3)
- Age  $\geq 18$  years and  $< 75$  years
- Body mass index (BMI)  $\geq 27$  kg/m^2
- Stable body weight during the previous 3 months ( $< 5$  kg self-reported weight change)
- Motivated for weight loss
- Achieved at least 5% weight loss during the initial 8-week IDI (assessed at allocation visit; T0)

In addition to this we required

- NGAL data at enrollment (week -8)
- Randomization (week 0)

Exclusion criteria in the original trial:

- On-going participation, or participation within the last 3 months, in an organized weight loss program (or within the last 3 months)
- Current or history of treatment with medications that may cause significant weight gain for at least 3 months before this trial
- Current use or use within 3 months before this trial of GLP-1 receptor agonist, pramlintide, sibutramine, orlistat, zonisamide, topiramate, or phentermine
- Type 1 diabetes
- Type 2 diabetes treated with glucose-lowering drugs other than metformin
- Arthroplasty in target knee joint (most symptomatic knee at screening)
- End stage disease in target knee joint (Kellgren-Lawrence grade 4)
- Immuno-inflammatory disease
- Chronic wide-spread pain
- Pregnancy or insufficient anti-conception therapy for female fertile patients
- Breast-feeding
- Estimated glomerular filtration rate (eGFR) < 60 ml/min/1.73 m^2
- Alanine aminotransferase (ALT) or aspartate aminotransferase (AST) > 3 x above upper normal range (UNR)
- Elective surgery scheduled during the trial duration period, except for minor surgical procedures
- Surgical procedures such as arthroscopy or injections into a knee within 3 months prior to enrollment
- Previous surgical treatment for obesity (excluding liposuction >1 year before trial entry)
- Thyroid stimulating hormone (TSH) outside of the range of 0.4-6.0 mIU/L
- Obesity secondary to endocrinologic or eating disorders, or to treatment with medicinal products that may cause weight gain
- Family or personal history of medullary thyroid carcinoma or multiple endocrine neoplasia type 2
- Inflammatory bowel disease

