## 8 ANALYSES

### 8.1 Outcome definitions

*Primary outcome:* Changes in serum NGAL following the 8-week intensive weight loss period (week -8 to week 0). Blood samples acquired from all participants at week -8 and 0 will be analyzed to determine serum NGAL (mg/ml). Plasma samples have been assessed using a commercially available electrochemiluminescence assay: NGAL/LCN2 R-plex Assay® produced by Meso Scale Discovery Inc (MSD), Rockville, Maryland, USA.

*Secondary outcomes:* Changes in serum NGAL in both liraglutide and placebo arm at week 0 and 52.

*Exploratory outcomes:* Changes in [i] CRP, [ii] total-Cholesterol, [iii] HDL, [iv] LDL, [v] TG, [vi] glucose, [vii] HbA1c, [viii] creatinine, [ix] eGFR, [x] ALAT, [xi] systolic BP, [xii] diastolic BP, [xiii] body weight and [xiv] BMI, in the two periods: enrollment to baseline (week -8 to week 0) and baseline to study end (week 0 to week 52).

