## 8.2 Analysis methods

The effect of the initial 8-week dietary intervention on the primary outcome variable serum NGAL will be analyzed using paired t-test. In the mITT population crude mean change will be estimated together with the associated 95% confidence interval and  $p$ -value corresponding to the test of the hypothesis of no difference between time points (i.e., the null hypothesis).

The effect of liraglutide and placebo (week 0 to 52) on the secondary endpoint change in serum NGAL will be determined using an ANCOVA model adjusted for stratification factors recorded at enrollment ([i]Sex, [ii] Age category and [iii] Obesity Class), and the level of the outcome at baseline (week 0). From this model, the observed differences in least squares means for change between liraglutide treatment and placebo will be estimated together with the associated 95% confidence interval and the  $p$ -value corresponding to the test of the hypothesis of no difference between treatments (i.e., the null hypothesis).

In the case of missing data at week 52, missing data will be handled using multiple imputations assuming data missing at random (MAR). A simple non-responder imputation (Enrollment Observation Carried Forward [EOCF]) will be done as a sensitivity analysis, assuming data missing not at random (MNAR).

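### A week -8 NGAL sample is required for every analysis, although the main week 0 to 52 NGAL comparison and the 28 exploratory analyses do not use that value

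*SAP*

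**What the plan says.** SAP section 6.2 is the only place where an analysis population is defined. It keeps all patients randomised at week 0 "regardless of their eligibility or adherence during the original trial but with NGAL data available at enrollment (week -8"), and adds: "This is a modified intention-to-treat (mITT) population of the original ITT population in the LOSE-IT trial". Section 7.2 lists "NGAL data at enrollment (week -8") as a further requirement on top of the original trial's criteria. No separate set is given for the secondary or exploratory outcomes.

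Section 8.2 analyses the secondary outcome, the week 0 to 52 change in NGAL, with an "ANCOVA model adjusted for stratification factors recorded at enrollment" (sex, age category, obesity class) "and the level of the outcome at baseline (week 0"). Section 8.1 lists 14 exploratory variables, NGAL not among them, to be analysed "in the two periods: enrollment to baseline (week -8 to week 0) and baseline to study end (week 0 to week 52").

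On missing data, section 8.2 plans multiple imputation for week 52 values and EOCF as a sensitivity analysis. The footnotes to Tables 2 and 3 also foresee multiple imputation. The titles of Table 2 and Appendix table 1 name the mITT population; those of Table 3 and Appendix table 2 name none.

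**The concern.** A condition that suits the primary outcome has been applied to everything. The paired change from week -8 to week 0 is informed directly only by patients with a week -8 NGAL value. The week 0 to 52 comparison starts from week 0. CRP, lipids, HbA1c, blood pressure, weight and the other exploratory outcomes do not involve NGAL at all. Yet a randomised patient who lacks one blood result from eight weeks before randomisation leaves all of these analyses, even with complete week 0 and week 52 data.

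The plan also treats missing values unevenly. A missing week 52 value is imputed, but a missing week -8 NGAL value removes the patient altogether, and the SAP gives no reason for the difference.

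At stake are the precision of the one randomised hypothesis in the plan (section 4.4, b) and of the 14 randomised exploratory comparisons, and their closeness to the full randomised set. Body weight matters most among these because it was a co-primary outcome of the original trial (section 5.4).

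**Working it through.** **1. Does each analysis use week -8 NGAL?** Sections 6.2 and 7.2 are set against 8.1, 8.2 and the table shells.

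| Analysis | Week -8 NGAL needed? |
|---|---|
| Primary: paired t-test of NGAL, week -8 to 0 | Yes, one half of each pair |
| Secondary: main NGAL ANCOVA, week 0 to 52 | No; the terms are treatment, three strata and week 0 NGAL |
| EOCF sensitivity analysis, NGAL rows (Appendix tables 1 and 2) | Yes, where a later NGAL value is missing |
| Exploratory, week -8 to 0 (14 outcomes) | No |
| Exploratory, week 0 to 52 (14 outcomes) | No |
| EOCF sensitivity analysis, other rows | No; each variable carries its own enrolment value |

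The exploratory count is 14 variables × 2 periods = 28 analyses, and week -8 NGAL enters none of them. The imputation model is not specified. It might use week -8 NGAL as a predictor, but that would not require the value to be observed.

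**2. The plan's own figure.** Section 5.4 gives 150 participants and more than 80% power for differences of 5.5 kg and 8 KOOS-Pain units. No standard deviation is given, so this cannot be reproduced. Working backwards with 75 per arm and a two-sided 5% level, SD = difference / [(1.960 + 0.842) × √(2/75)]. Exactly 80% power corresponds to SDs of 12.02 kg and 17.49 units. The point does not depend on these figures. The SAP gives no power for NGAL and no size for the mITT set.

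**3. Cost of the rule.** The number of randomised patients without week -8 NGAL is not stated, so an excluded fraction m is assumed. The interval widens by the factor 1/√(1 − m). Power for a comparison that would have exactly 80% at 75 per arm is Φ[√(1 − m) × (1.960 + 0.842) − 1.960].

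| Assumed m | Patients lost of 150 | CI width factor | Power |
|---|---|---|---|
| 0% | 0 | 1.000 | 80.0% |
| 2% | 3 | 1/√0.98 = 1.010 | 79.2% |
| 5% | 7 to 8 | 1/√0.95 = 1.026 | 78.0% |
| 10% | 15 | 1/√0.90 = 1.054 | 75.7% |

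These are upper bounds. An excluded patient costs full precision only if that patient has both the week 0 and the week 52 value of the outcome.

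**The case against.** The strongest defence is that one common cohort is a sensible choice for a paper about NGAL. Table 1 describes a single set, and Figure 2 shows NGAL and BMI side by side, so changes in weight or CRP can be read against changes in NGAL in the same people. The plan also calls itself exploratory (section 6.1), and the loss of precision is small. The modest size is conceded. The common-cohort argument is not made in the SAP, and it does not explain why randomised patients should leave treatment comparisons that do not involve NGAL.

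Three stronger readings are tempting and are not supported:

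- *That the rule biases the treatment comparison or abandons intention-to-treat.* The week -8 sample precedes randomisation, so treatment cannot influence who is selected. Patients stay in whatever their eligibility or adherence, and the set is openly labelled as modified.
- *That week -8 NGAL has no role in the randomised NGAL comparison.* It has one in the EOCF sensitivity analysis. Section 7.3 reports 14 + 13 = 27 patients lost to follow-up after randomisation (27/150 = 18% if 150 were randomised), so carrying forward may not be rare. Admitting patients without week -8 NGAL leaves EOCF undefined for any who also lack week 52 NGAL, and the fix must deal with this.
- *That the weight result will conflict with the published one.* The original analysis set, model and estimates are not in this document, so this cannot be checked.

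**Conclusion.** The point holds in a limited form. As written, sections 6.2 and 7.2 require week -8 NGAL for every analysis, while only the primary paired change and the NGAL rows of the EOCF analysis need it. The case is clearest for the 14 randomised exploratory comparisons. It is weaker for the secondary NGAL outcome, where the value does serve the sensitivity analysis. The consequence is some lost precision and a set smaller than the one randomised: intervals up to about 1%, 2.6% or 5.4% wider at an assumed 2%, 5% or 10% excluded, and no cost if nobody lacks the sample. The assumptions are that about 150 patients were randomised, that exclusions fall equally on the two arms, and that the restriction also governs Table 3 and Appendix table 2, whose titles name no population. The last follows from section 6.2 defining only one.

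**What to change.** In sections 6.2 and 7.2:

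- Keep the week -8 NGAL requirement for the primary paired analysis only.
- For the week 0 to 52 comparisons (NGAL and the 14 exploratory outcomes), analyse all randomised patients as randomised, with missing values handled by the planned multiple imputation.
- For exploratory changes from week -8 to 0, drop the NGAL condition and use all randomised patients who have that outcome's own week -8 value.
- State that the EOCF analysis of NGAL in Appendix table 2 covers patients who have week 52 NGAL or a week -8 NGAL value to carry forward.
- Name the population and N in every table and in Figure 1.

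The cost is a few lines of text and some population flags. N may differ between tables and, for the week -8 to 0 changes, between outcomes. The EOCF analysis of NGAL may have a slightly smaller N than the main one. A patient with no NGAL value at any visit would enter the main NGAL analysis through imputation alone and add almost no information. If every randomised patient has a week -8 NGAL sample, the results do not change.

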## **7 TRIAL POPULATION**

### **7.1 Screening data:**

Not used in the current study.

### **7.2 Eligibility**

Inclusion criteria in the original trial as described in suppl. material *Am J Clin Nutr* 2021;**113**:314–23. doi:10.1093/ajcn/nqaa328 [2]:

- Informed consent obtained
- Clinical diagnosis of knee OA (American College of Rheumatology [ACR] criteria) with early to moderate radiographic changes (Kellgren-Lawrence [KL] grades 1, 2, or 3)
- Age  $\geq 18$  years and  $< 75$  years
- Body mass index (BMI)  $\geq 27$  kg/m^2
- Stable body weight during the previous 3 months ( $< 5$  kg self-reported weight change)
- Motivated for weight loss
- Achieved at least 5% weight loss during the initial 8-week IDI (assessed at allocation visit; T0)

In addition to this we required

- NGAL data at enrollment (week -8)
- Randomization (week 0)

Exclusion criteria in the original trial:

- On-going participation, or participation within the last 3 months, in an organized weight loss program (or within the last 3 months)
- Current or history of treatment with medications that may cause significant weight gain for at least 3 months before this trial
- Current use or use within 3 months before this trial of GLP-1 receptor agonist, pramlintide, sibutramine, orlistat, zonisamide, topiramate, or phentermine
- Type 1 diabetes
- Type 2 diabetes treated with glucose-lowering drugs other than metformin
- Arthroplasty in target knee joint (most symptomatic knee at screening)
- End stage disease in target knee joint (Kellgren-Lawrence grade 4)
- Immuno-inflammatory disease
- Chronic wide-spread pain
- Pregnancy or insufficient anti-conception therapy for female fertile patients
- Breast-feeding
- Estimated glomerular filtration rate (eGFR) < 60 ml/min/1.73 m^2
- Alanine aminotransferase (ALT) or aspartate aminotransferase (AST) > 3 x above upper normal range (UNR)
- Elective surgery scheduled during the trial duration period, except for minor surgical procedures
- Surgical procedures such as arthroscopy or injections into a knee within 3 months prior to enrollment
- Previous surgical treatment for obesity (excluding liposuction >1 year before trial entry)
- Thyroid stimulating hormone (TSH) outside of the range of 0.4-6.0 mIU/L
- Obesity secondary to endocrinologic or eating disorders, or to treatment with medicinal products that may cause weight gain
- Family or personal history of medullary thyroid carcinoma or multiple endocrine neoplasia type 2
- Inflammatory bowel disease
- Congestive heart failure, New York Heart Association (NYHA) class III-IV
- Diabetic gastroparesis
- History of or current diagnosis of pancreatitis (acute and/or chronic) or pancreatic cancer
- History of cancer with the exception of in-situ malignancies of the skin or cervix uteri
- History of major depressive disorder, a PHQ-9 (Patient Health Questionnaire-9) score of more than 15, or a history of other severe psychiatric disorders or diagnosis of an eating disorder
- Subjects with a lifetime history of a suicide attempt or history of any suicidal behavior within the past month before entry into the trial
- Inability to speak Danish fluently
- A mental state impeding compliance with the program
- Use of opioids or similar strong analgesics
- Allergic reactions to the active ingredients of Saxenda, such as hypotension, palpitations, dyspnea and edema

